### Eligibility criteria

The target group of this study is children aged four to 12 years who display symptoms of internalizing and/or externalizing problems, and their parents. Participants are excluded if; (a) the child is referred to, or receives, treatment in the specialist services for child and adolescent mental health (BUP) for problems within the internalizing or externalizing domains, (b) the child is diagnosed with pervasive developmental disorder, post-traumatic stress disorder or psychosis, (c) the child exhibit signs of acute risk for suicide, (d) there is documented or suspected ongoing physical or sexual abuse, or (e) the child or the parents receive other systematic interventions targeting the inclusion criteria at the time of recruitment and during the study period. All participating municipalities have implemented PMTO and the PMTO short-form Brief Parent Training for externalizing problems. Since SPARCK partly includes PMTO-based components, neither PMTO-based interventions can be provided as condition 1 intervention, as we would run the risk of evaluating similar content in both conditions for a large proportion of participating families.

### Retention and project implementation

To ensure successful implementation of the study, the host organization (NUBU) collaborates on data collection with local study coordinators in each participating municipality. The study coordinators at the host organization *oversee* the recruitment and data collection process at all the 24 sites. This includes activities concerning the externally provided randomization module, distribution and collection of research data, and to provide support to local study coordinators in the municipalities. The local study coordinators handle the practicalities in the participant recruitment, administers randomization results, organizes practitioners, monitors intervention start-up and end dates in both conditions, monitors data collection, and provides relevant study information to municipal frontline services. The host organization researchers and clinical personnel are not directly involved in the data collection. However, a NUBU core group of researchers and clinical personnel will assist the frontline services when they need research study assistance. For example, problem solving, consideration of eligibility criteria in specific cases, when to discontinue intervention in cases where symptoms are worsening, and to provide information to leaders. Furthermore, the core group will conduct ongoing audits of the trial based on information provided by the collaborating sites and SPARCK supervisors.

To further mitigate the risk of potential harm resulting from participants receiving SPARCK in the study, we have implemented several measures. Firstly, we will conduct an interim data inspection halfway through data collection period to evaluate the quality of the data collected thus far. A data monitoring committee will be supervised by an external researcher who is not involved in the project, and who will oversee the data inspection process and make any necessary decisions. In addition, during the interim data inspection, we will evaluate the balance of the study design in terms of internalizing and externalizing symptoms. If the data reveals any imbalance, we will review the research questions and hypotheses accordingly, to ensure that our analysis is appropriately informed by the data collected.

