We posit several hypotheses to guide the investigation of SPARCK. More specifically, our primary hypothesis is: H1: Children of parents receiving SPARCK will exhibit lower levels of internalizing and/or externalizing symptoms compared to those who receive UC at a) the end of the intervention and b) 6 months post-intervention. Our secondary hypotheses are: H2: Parents in the SPARCK condition will demonstrate better parenting practices, self-efficacy, and less parental stress than parents in the UC condition at a) the end of intervention and b) 6 months post-intervention; and H3: The effect of SPARCK on child symptoms is mediated by changes in parenting practices; H4: Children (≥ 7 years) and parents in the SPARCK condition will report better subjective quality of life than children (≥ 7 years) and parents in the UC condition; H5: Among those who display abnormal blunted or elevated stress hormone levels as indicated by cortisol and DHEA at pre-intervention, children and parents in SPARCK will be more likely to change towards normative levels at post-intervention than those who receive UC; H6: Children in the SPARCK condition will display lower levels of school refusal than children in the UC condition at a) the end of intervention and b) 6 months post-interventions; and H7: Children in the SPARCK condition will be less likely to be referred to child and adolescent outpatient clinics (Norwegian abbreviation: BUP) or have contact with the Child Welfare Services (CWS) in the following two years compared to children in the UC condition.

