### Measures

Various measurement instruments are used to investigate the primary hypothesis of parent reported change in child externalizing and internalizing symptoms. and the secondary hypotheses testing various outcomes such as change in proximal family relational outcomes, and other more distal child and parent level outcomes, including moderators, mediators and background factors. An overview of assessment instruments is displayed in Table 1.

**Table 1 Tab1:** Measurement instruments

Measures	Respondent	Level outcome	T1	T2	T3	T4	Weekly assessed
ECBI	Parent	Child	x	x	x		
RCADS-P	Parent	Child	x	x	x		
SDQ-P	Parent	Child	x	x	x		
SRQ	Parent	Child	x	x	x		
Kid-KINDL	Child	Child	x	x^1^			
PAFAS	Parent	Relational	x	x	x		
FRQ	Parent	Relational	x	x	x		
PAB	Parent	Relational	x	x	x		
MaaP-SF	Parent	Parent	x	x	x		
PSS	Parent	Parent	x	x	x		
SWLS	Parent	Parent	x	x	x		
HSCL-10	Parent	Parent	x	x	x		
LES	Parent	Parent	x	x	x		
BioM	Child	Child	x	x^1^			
BioM	Parent	Parent	x	x^1^			
PRQ	Practitioner	Service & Intervention	x	x			
FidQ	Practitioner	Intervention					x
WAI-S	Practitioner	Intervention		x			
WAI-S	Parent	Intervention		x			
UserSQ	Parent	Intervention		x			
RBD	Registers	Child				x	

The parent questionnaires take approximately 20 min to complete. Parents receive 200 NOK (approximately 20 USD) as compensation for the time spent completing the questionnaires and providing hair samples. Instruments with positively formulated items are strategically interspersed among the instruments with negatively formulated items.

For the primary outcome on externalizing problems at T1-3, we will use the parent reported Eyberg Child Behavior Inventory intensity scale (ECBI; [60]) which assesses frequency of children’s externalizing symptoms. For the primary outcomes on internalizing symptoms, we will use the Revised Child Anxiety and Depression Scale parent version (RCADS-P; [61]). In addition, as this is a community level sample with heightened, but not clinical level, symptoms, and may include both children with externalizing and/or internalizing problems, we include the Strengths and Difficulties Questionnaire parent report (SDQ-P). The 20-item total problem scale from the SDQ-P, which assesses multiple correlates of internalizing and externalizing symptoms in children, is included as a primary outcome [62].

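### The mid-trial review of hypotheses is not limited to pooled baseline data, so the wording permits H1 to change after outcome data have been seen

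*Protocol article*

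**What the plan says.** All of the operative text is in the protocol article, Methods, under Retention and project implementation. The team announces that "we will conduct an interim data inspection halfway through data collection period to evaluate the quality of the data collected thus far". The committee that monitors the data is supervised by an external researcher with no part in the project, "who will oversee the data inspection process and make any necessary decisions". In the same inspection, "we will evaluate the balance of the study design in terms of internalizing and externalizing symptoms". The consequence follows: "If the data reveals any imbalance, we will review the research questions and hypotheses accordingly", and the stated purpose is "to ensure that our analysis is appropriately informed by the data collected".

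The primary hypothesis is under Aims and research questions: "Children of parents receiving SPARCK will exhibit lower levels of internalizing and/or externalizing symptoms compared to those who receive UC", at the end of the intervention and six months later. Measures names three primary outcomes: the ECBI intensity scale for externalizing problems, the RCADS-P for internalizing symptoms, and the SDQ-P total problem scale.

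**The concern.** The quantities inspected at mid-trial are the two symptom domains that make up H1 and that the primary outcomes measure. A review of hypotheses prompted by them therefore bears directly on the confirmatory question. H1 joins the domains with and/or, so a shift of emphasis to one domain would be easy to make and hard to detect afterwards.

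What is at stake is the confirmatory status of the primary result. A hypothesis that is altered after half the data collection, and then tested on the same families, is confirmatory only if the information behind the change was unrelated to the treatment effect. The protocol does not secure that condition. Once the inspection has taken place, a reader will be unable to tell which data prompted any change. This is a stated rule rather than a detail left to an analysis plan: a plan that froze H1 would have to override this sentence.

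**Working it through.** No figure in the protocol bears on this point. The sample size calculation under Data analyses (164, then 252) is not affected by it. The check is therefore a reading of the text, followed by an illustration.

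**1. What the text restricts.**

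| Question | What the protocol says |
|---|---|
| Which time points are inspected? | Not limited. Data quality refers to everything collected so far; the balance check names symptoms, not T1. |
| Pooled or by arm? | Not stated. |
| What counts as imbalance? | Any; no threshold. |
| Which hypotheses may be reviewed? | Research questions and hypotheses in general; H1 is not exempted. |
| Who reviews them? | The team ("If the data reveals any imbalance, we will review the research questions and hypotheses accordingly"), although an external researcher oversees the inspection. |

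**2. Could outcome data exist at that point?** Under Data collection, T2 is taken at the end of treatment and at the latest 25 weeks after T1. Any family whose T1 lies more than 25 weeks before the inspection should have T2 data. The length of the collection period is not given, so the share of families cannot be computed, but some T2 data are likely to exist.

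**3. Do the blinding statements elsewhere close the gap?** Participants, recruitment, and randomization conceals the allocation sequence and tries to keep families from knowing their condition. Data management gives researchers de-identified data. None of these says that those who inspect the data are blind to arm.

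**4. The harmless case.** T1 is completed before randomization. A choice between outcomes based on pooled T1 scores carries no information about the treatment effect. Simulating 1,000,000 null trials in which the outcome is chosen without reference to the treatment difference gives a two-sided type I error of 5.0% at a nominal 5%.

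**5. An illustration of the harmful case.** Assumptions, none taken from the protocol: K null z-statistics with common correlation r; the outcome most favourable to SPARCK at information fraction t becomes the tested hypothesis; the final test is z > 1.96 on all data. With z₁ from the first part and z₂ from the second, the final statistic is z = √t·z₁ + √(1−t)·z₂. False claims in favour of SPARCK, against 2.5% for one outcome fixed in advance, are:

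- t = 0.5, r from 0.7 down to 0: 3.7 to 4.6% with K = 2, and 4.6 to 6.3% with K = 3.
- t = 0.2 to 0.3, r from 0.5 down to 0: roughly 3.5 to 4% with K = 2, and roughly 4 to 5.5% with K = 3.

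**6. What the comparator should be.** The 2.5% baseline holds only if H1 is otherwise controlled at that level. If any one of three independent outcomes at z > 1.96 counted as success, the chance of a false favourable claim would already be 1 − 0.975³ = 7.3%; with two it is 1 − 0.975² = 4.9%. At r = 0.5 simulation gives about 6.3% and 4.6%. These exceed the corresponding figures in step 5, so the size of any rise depends on how multiplicity under H1 is handled. The article does not state this, and an analysis plan may settle it.

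**The case against.** The strongest reply is that the check concerns case mix. Under Participants, recruitment, and randomization, families enter on clinical judgement without a standardized assessment, so the symptom mix is unknown until data arrive. The Discussion explains why the mix matters: where a child lacks one type of symptom, that outcome can dilute the effect on the type the child does have. Neither section speaks of choosing the domain in which SPARCK looks better. This is the more natural reading, and under it there is no inflation if only pooled T1 data are used.

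Two further points have force. The protocol commits to a review that depends on a finding of imbalance, and such a review may leave everything unchanged. An uninvolved external researcher also oversees the inspection and has authority to decide.

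These points limit the concern but do not remove it. The benign reading is nowhere written down, and the stated purpose, "to ensure that our analysis is appropriately informed by the data collected", is wider than a description of case mix. The external researcher's authority attaches to the inspection; it does not freeze H1, and the review of hypotheses is given to the team.

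A reader might go further and infer that the hypotheses will be revised, that the team intends to pick the better-looking domain, or that the error rate will rise by a definite amount. The documents support none of these. The text says review, the trigger is symptom balance rather than an effect estimate, and the pick-the-best rule and the information fractions above are assumptions.

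**Conclusion.** The point holds as a defect of wording with possible consequences for the primary hypothesis. The sentence permits, but does not require, a change to H1 or its primary outcomes after outcome data have been seen, and no other statement in the article prevents this. The effect on type I error ranges from none, if only pooled T1 scores are viewed, to an increase that the document does not determine if outcomes by arm are visible. The simulated percentages illustrate a selection rule that the protocol does not contain and should not be cited as this trial's error rate. The conclusion assumes only that some T2 data exist at the inspection and that the sentence is followed as it stands. It should be settled before the inspection, because afterwards the origin of any change cannot be demonstrated.

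**What to change.** Rewrite the sentence under Retention and project implementation to say three things:

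1. The balance check uses only T1 symptom scores, pooled over arms and without arm labels.
2. H1 and its three primary outcomes stay as the protocol states them, whatever the check shows.
3. Any hypothesis changed or added after the inspection is recorded in a dated amendment and reported as exploratory.

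The cost is a few sentences in the protocol and the matching text in the analysis plan and the committee's remit. No additional families or data are needed. The one real downside is small: the team gives up the freedom to re-target its confirmatory hypotheses if the symptom mix turns out differently from what it expects.

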### Intervention conditions

#### Condition 1: Usual care

The UC condition refers to the standard clinical practice in the Norwegian frontline services, which varies in scope and intensity across different municipalities. In total, the 24 municipal sites have listed 23 manualized interventions that are planned to be used as UC, in addition to un-structured counselling. Eleven out of the 23 manualized interventions can be deemed evidence-based, supported by empirical documentation of intervention effectiveness. The median number of potential manualized UC interventions per municipality is three. Two municipalities have only listed un-structured counselling with professional practitioners as UC, whereas 23 have listed unstructured counselling in addition to manualized interventions. In line with the heterogenic Norwegian frontline service system, the practitioners in both the UC and SPARCK condition will vary in background training and clinical competence. Professions listed by the 24 municipalities include public health nurse, social worker, psychologist, educational psychological counsellor, and physician.

In the UC condition, intervention can be given to the parents, to the child or to a combination of parents and child – either together in sessions or sequential. There is no minimum or maximum number of sessions or weeks in the UC condition.

#### Condition 2: SPARCK intervention

SPARCK is a transdiagnostic preventive intervention designed to target both internalizing and externalizing problems. The primary objective is to enhance developmentally appropriate parenting practices that may foster sensitive parent–child relationships and nurture the fundamental core skills necessary for healthy child development. A conceptual model of the SPARCK theory of change (ToC) is displayed in Fig. 2.

**Fig. 2 Fig2:**
[figure not shown]
Conceptual model of the SPARCK theory of change

SPARCK is designed to be delivered in up to 12 weekly 1-h individual face-to-face sessions, ideally attended by both parents. If deemed necessary, the practitioner and family can decide together to adjust this plan, for instance to have longer intervals between sessions (excluding the introductory sessions), or to have online sessions. The first step in the SPARCK intervention, the Mapping component, is fundamental for the customization of intervention components to the families’ needs. During this session, parents collaborate with practitioners to make clear and concise goals in intervention (see Fig. 2). Importantly, the goals (maximum three) must include child and/or parent behavior and/or parent–child interactions that are amenable to change (e.g., *Child goes to sleep in own bed; We as parents stay calm when helping with homework)*. The parents` goals, together with information from any referral papers and assessments carried out prior to and during the Mapping session, are used to get a picture of the strengths and challenges experienced by the families and to choose what appears to be the primary problem that should be addressed first.

The various components outlined in Fig. 2 include a broad range of intervention strategies for parents to use in their daily interactions with their children. The components typically begin with sharing knowledge, for instance on the importance of emotional validation for emotion regulation, the rationale for exposure, and the value of predictable routines for child well-being. Further, the components outline examples of helpful questions to engage the families and make the topic relevant. Additionally, all components include role plays to model and practice specific skills, such as how to validate the child`s emotion, give directions, or ways to talk with the child about exposure. A central part of many components is a description of how to develop a step-by-step plan tailored to each family`s specific goals. All components also include examples of homework assignments. Essentially, SPARCK can be conceptualized as a parent training intervention by targeting child symptoms via change in parent–child interactions and parenting behaviors. However, SPARCK also incorporates components that can be seen as parent-led CBT, such as the parent-led Exposure component.

To help the SPARCK practitioner make the choices of components that may fit the family’s needs, a Decision support system (DSS) consisting of four recommended tracks outlines which components to use and in what order. The recommended tracks target 1) anxiety symptoms, 2) depression symptoms, 3) conduct problems, and 4) caregiving challenges. For example, the DSS recommended track for addressing anxiety issues involves Mapping, Emotional validation, Psychoeducation anxiety, and Exposure and/or Family accommodation. Additionally, the DSS provides guidance on when to incorporate other components. Even if the family reports multiple concerns, a recommended track is still to be chosen to ensure a clear focus. To allow for this flexibility, SPARCK components are designed as stand-alone components, allowing practitioners to choose and combine them throughout the course of intervention. However, there is a sequential nature of the components, advising that the SPARCK practitioners should adhere to a prescribed order. For example, Emotional validation and Psychoeducation anxiety should be addressed before parental supported Exposure, while Good directions and Rewards before Limit setting. Parents are given the option of bringing the child to a session at the beginning of the course of intervention to provide the child with information about SPARCK, as well as the opportunity to share any wishes for change. If considered necessary, the parents may also bring the child to a subsequent session (e.g., for psychoeducation, brainstorming or to practice specific skills). Any inclusion of the child is always conducted jointly with their parents.

The SPARCK practitioners work in the municipal frontline services and thus have comparable training and educational background to the practitioners in the control condition. However, all SPARCK practitioners have previously undergone training in PMTO. The SPARCK training of practitioners consists of a four-day training program that familiarize the practitioners with the content of SPARCK. Furthermore, the training program includes a weekly one-hour supervision session for pairs of SPARCK practitioners during their first two cases. For subsequent cases, supervision dosage is reduced to one hour every second week for the pairs of SPARCK practitioners. The initial weekly supervision is part of the SPARCK training and enables a more practical form of learning the content, that is, through discussion of issues that arise along the course of sessions with the parents. The SPARCK practitioners will receive supervision from specialists in clinical psychologists from NUBU or from members of the host organizations’ National Implementation Team, all of which have undergone previous training in and practice with SPARCK.

### Data collection

In this study we use a combination of web-based questionnaires to be completed by one parent on mobile phones, pen-and-pencil questionnaires to the children for those who are seven years or older, and hair samples from one parent (i.e., the parent who answers the questionnaires) and the child to measure biomarkers of stress (i.e., cortisol and DHEA). The families receive a hair-sample kit with instructions and necessary equipment for cutting the correct amount of hair. The pen-and-pencil questionnaires for the children is distributed together with the hair-sample kits.

Parent reported data (i.e., the web-based questionnaires by one parent) will be gathered at three time points; pre (T1), post (treatment termination, T2), and six months follow-up (six months after post, T3; see Fig. 1). If the UC group receives open-ended treatments or counselling is delayed in either condition, we will gather T2 parent reported data at 25 weeks after T1 (i.e., T2 is gathered 25 weeks after T1 at the latest). Hair samples will be gathered through participant self-sampling from one parent and the child in all families. Both the hair samples and the child report pen-and-pencil questionnaire is gathered in connection with T1 and at T2. They are instructed to send a text message to the NUBU study coordinators when they have posted the hair-samples and the child questionnaire in the mail, upon which they are ready to be randomized. At T2, the hair-sample kit and the child questionnaire are sent out approximately four weeks after the termination of the intervention (or two weeks after week 25). The delay in the data gathering of hair-samples is simply because the hair-samples reflect the retrospective average bio-marker levels across an 8-week period (two-centimeter hair segment samples).

Finally, register data from Statistics Norway for CWS service contacts and from the Norwegian Patient Register for service referrals will be collected. Data will be obtained two years after post-treatment. Parents have consented to collection of register-data up to 5 years after follow-up, but the potential five-year long-term register data collection depends on the project receiving additional funding.

